- Weight gain (g / kg / day), defined as the difference in weight (g) from admission to week 4, to week 8 and to discharge divided by weight on admission (kg) and number of days between admission and week 4/week 8/discharge among recovered children.
  - Defaulting, defined as 3 missed scheduled facility visits in the weekly follow-up group and 1 missed scheduled facility visit in the monthly follow-up group.
  - Relapse, defined as maternal report of admission to any therapeutic feeding program within 3 months of discharge from the index admission.
  - Program coverage, defined as single coverage of SAM treatment, estimated in the weekly and monthly follow-up groups using the SQUEAC methodology.
  - Cost per child treated and per child recovered, defined using the societal perspective to identify all provider and caregiver costs associated with treatment.

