### 3.4 Target population

The study subjects will be children newly admitted for the treatment of uncomplicated SAM at one of 10 outpatient therapeutic feeding centers.

The specific eligibility criteria for the treatment of uncomplicated SAM:

- age from 6 to 59 months
- MUAC < 115 mm and/or grade 1-2 edema
- Absence of current illness requiring inpatient care\*

\*As per current treatment protocols, children will be referred to inpatient care if presenting with lack of appetite, intractable/continuous vomiting, fever, hypothermia, lower respiratory tract infection, severe respiratory distress, any chest in-drawing, severe anemia (hemoglobin < 7 g/dl), skin infection or lesions requiring IM/IV treatment, altered consciousness, hypoglycaemia, convulsions, severe dehydration, presence of grade 3 edema.

The specific inclusion criteria for the study are:

- Eligible for new admission\*\* at one of the study outpatient therapeutic feeding centers
- Written informed consent of parent or legal guardian

\*\*New admissions include cases of relapse, where the child was previously successfully treated, discharged as cured and returns with a new episode of acute malnutrition within 2 months of discharge. New admission will include children transferred from inpatient care to outpatient care to continue treatment but does not include children transferred from another outpatient site. New admission does not include returned defaulters who were absent for 3 consecutive visits before recovery and return to continue treatment.

The specific exclusion criteria for the study are:

- History of allergy to peanuts
- Any other condition in which, in the judgment of the Field Investigator, would interfere with or serves as a contraindication to protocol adherence or the ability to give informed consent\*\*\*

\*\*\*While determining eligibility, study staff will be asked to use good clinical judgment in considering a participant's overall suitability for inclusion. Some participants may not be appropriate for the study even if they meet all inclusion criteria. For instance, medical,

occupational or other conditions of the participant or parent/guardian may make routine home visits and evaluation difficult or make the child a poor candidate for retention. Any such potential exclusion must be validated by the Field Investigator.

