#### 4.9 Post-discharge follow-up

All children will receive a home visit by a community health worker 3 months following discharge from the nutritional program, regardless of type of discharge (e.g. recovered, default or non-recovered), requesting the caregiver and child to return to the outpatient therapeutic center. At each post-discharge visit, anthropometric measures (e.g. weight, height and MUAC) will be taken; history of nutritional treatment within the last 3 months will be assessed by maternal report; and caregivers knowledge, attitudes and practices related to the key danger signs and MUAC assessment will be assessed by standardized questionnaire (see Annex 9.2). Compensation (e.g. 2 pieces of soap) for participation in the post-discharge visit will be provided to caregivers at the end of the visit.

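### The relapse endpoint has no prior-recovery condition and ignores the MUAC measured at 3 months, so resumed treatment can count as relapse, possibly to a different extent in each arm

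*Protocol*

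**What the plan says.** - **Endpoint.** Protocol section 2.0 gives: "Relapse, defined as maternal report of admission to any therapeutic feeding program within 3 months of discharge from the index admission". The abstract's list of outcome variables carries the same definition, so the wording is deliberate. Neither place states a recovery condition or an anthropometric criterion.
- **Who is followed.** Section 4.9 provides the 3-month visit "regardless of type of discharge (e.g. recovered, default or non-recovered"). Default and non-recovery are thus named as types of discharge.
- **What is collected at that visit.** Section 4.9 states that "anthropometric measures (e.g. weight, height and MUAC) will be taken" and that "history of nutritional treatment within the last 3 months will be assessed by maternal report". Only the second item enters the endpoint.
- **Relapse elsewhere in the protocol.** The eligibility footnote in section 3.4 applies the term to a child "discharged as cured and returns with a new episode of acute malnutrition within 2 months of discharge".
- **Returning defaulters.** The same footnote adds: "New admission does not include returned defaulters who were absent for 3 consecutive visits before recovery and return to continue treatment".
- **Default rule.** Section 2.0 requires three missed visits in the weekly arm and one in the monthly arm. Section 4.8 adds that the three must be consecutive. Section 4.8 also has a community health worker ask the caregiver to bring the child back after any missed visit, in both arms.
- **Analysis.** Section 3.9 applies intention to treat to all analyses. It limits weight gain to recovered children but sets no such limit for relapse.

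**The concern.** Relapse ordinarily means a new episode after recovery, and section 3.4 uses it that way. The endpoint leaves the recovery condition out, so it can mix three things: a new episode after cure, resumption of an unfinished course after default, and further treatment of a child who never recovered. It also cannot register a child who is again severely malnourished by the trial's own MUAC threshold when measured at 3 months but has not been readmitted.

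The mixing need not be equal between arms. A monthly-arm child who misses one visit and comes back a week later has met the default definition, while a weekly-arm child who does the same has only been absent. At stake is the interpretation of one secondary objective, the comparison of relapse within 3 months of discharge. The primary endpoint definition and the power calculation do not depend on it.

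**Working it through.** The protocol gives no relapse rate, default rate or power for this endpoint, so there is no stated figure to reproduce. The check is a reading of the text followed by an illustration on assumed rates.

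**Reading the sections together**

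| Child | Endpoint as written (2.0, 4.9) | Section 3.4 sense of relapse |
|---|---|---|
| Recovered, readmitted at week 6 after discharge | Relapse | Relapse |
| Recovered, readmitted at week 11 after discharge | Relapse (3-month window) | Outside the 2-month window |
| Defaulted, resumes treatment within 3 months | Not excluded; can be reported as an admission | Not relapse |
| Non-recovered, admitted again within 3 months | Not excluded | Not relapse |
| Recovered, MUAC below 115 mm at 3 months, not readmitted | Not relapse | Not addressed (footnote concerns children presenting for admission) |

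**How far the default rule alone can separate the arms**

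Assumptions: 8 weeks of treatment (8 weekly visits; 2 monthly-arm visits, at weeks 4 and 8); each visit missed independently with probability m; the same m in both arms.

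- Monthly, at least one miss of two: 1 − (1 − m)². At m = 0.05 this is 1 − 0.9025 = 9.75%; at m = 0.10 it is 1 − 0.81 = 19.0%.
- Weekly, three consecutive misses in eight (section 4.8), summing over the visit at which the first run of three ends: 0.07% at m = 0.05 and 0.55% at m = 0.10.
- Weekly, any three misses in eight (section 2.0), binomial tail P(X ≥ 3): 0.6% at m = 0.05 and 3.8% at m = 0.10.

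Over the full 12 weeks (12 visits against 4) the corresponding ranges are 18.6–34.4% monthly, and weekly 0.12–0.91% (consecutive) or 2.0–11.1% (any three).

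If half of defaulters resume care within 3 months and report it as an admission (assumed), the 8-week figures give 4.9–9.5 points of apparent relapse in the monthly arm. The weekly arm has 0.04–0.27 points (consecutive) or 0.3–1.9 points (any three).

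**Effect on the arm difference**

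Let d be the default proportion, r the readmission proportion among non-defaulters (equal in both arms), and q the share of defaulters who return. Then

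reported relapse = (1 − d)·r + d·q,

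so monthly minus weekly = (d_monthly − d_weekly)·(q − r).

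With assumed default of 20% monthly and 10% weekly, and q from 0.25 to 0.75:

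- r = 5%: 0.10 × (0.20 to 0.70) = +2.0 to +7.0 points.
- r = 10%: 0.10 × (0.15 to 0.65) = +1.5 to +6.5 points.

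With 10% monthly and 20% weekly the signs reverse. With equal default the difference is zero. Among non-defaulters alone it is zero by construction, since r is the same in both arms.

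**Missed cases**

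If 5–10% of children are readmitted and a further 2–10% are severely malnourished at 3 months without readmission (both assumed), the endpoint captures r/(r + u), where u is the second proportion. This runs from 0.05/0.15 = 33% to 0.10/0.12 = 83% of those back in severe acute malnutrition.

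**The case against.** The strongest reply is that section 3.4 already separates returned defaulters, who continue treatment, from new admissions, and that section 4.8 asks traced children back for their scheduled follow-up. On that reading a return is not an admission and never reaches the endpoint. This stands in part: the text does not say that a returning defaulter counts as a relapse, only that nothing excludes one. It does not remove the point. The footnote governs study inclusion, it describes three consecutive absences, which is the weekly rule and does not fit a monthly defaulter, and the endpoint rests on what the mother reports.

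A second reply is that section 4.9 sets a visit schedule, not an analysis population, and that the population may be left to an SAP. That is fair as far as the denominator goes. The endpoint definition itself, however, is fixed in the protocol, and section 3.9 states a recovered-only limit for weight gain but not for relapse.

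Third, reported readmission covers the whole interval, whereas one MUAC at 3 months misses episodes treated and resolved earlier. This is correct, and it is a reason to use both sources.

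Fourth, the illustration assumes independent misses at equal rates. Families who stop attending miss visits in sequence, which raises weekly default, and monthly attendance may be better because the burden is lower. This also stands: the figures show a mechanism and do not predict the trial's result.

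**Conclusion.** The point holds as a defect in the definition of a secondary endpoint. As written, relapse can include resumed treatment after default or non-recovery and cannot include severe malnutrition measured at 3 months without readmission. The arm-specific default rules make differential misclassification possible. On the assumed rates the distortion runs from about 1.5 to 7 points in either direction when default differs by 10 points, and is zero when default is equal.

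A reader might infer three stronger things that the protocol does not support.

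- That the monthly arm is necessarily biased upward. The direction depends on attendance and return rates that the protocol does not give.
- That the relapse objective cannot be answered. MUAC and treatment history are collected at the 3-month visit whatever the type of discharge, so a recovered-only analysis needs no new design.
- That relapsed study children will be counted twice in the primary analysis. Section 3.4 treats relapses as new admissions and nothing expressly bars re-enrolment, but no section plans it. This is a minor point to close.

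**What to change.** 1. Define relapse among children discharged as recovered, as reported readmission in the 3-month interval or MUAC below 115 mm at the 3-month visit (or oedema, if it is checked there).
2. Report readmission or return after default or non-recovery separately, by arm.
3. Keep readmission among all enrolled children, by randomised arm, as a separately named outcome. Restricting to recovered children conditions on a post-randomisation outcome, and the all-children version shows whether that matters.
4. Reconcile sections 2.0 and 3.4 on what relapse means and on the 2-month and 3-month windows, and state whether a returning defaulter in each arm is recorded as a readmission or as continued treatment.
5. As a minor addition, state that only each child's first enrolment enters the analysis.

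The cost is mainly wording. MUAC is already measured at the visit. Oedema is not named among the measures in section 4.9 and would need a brief check. The downside is a smaller denominator for the recovered-only endpoint, together with the conditioning that item 3 addresses.

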### 3.0 METHODOLOGY

#### 3.1 Study design

This study will be conducted as a stratified cluster randomized trial of a monthly schedule of follow up in the treatment of uncomplicated SAM among children aged 6 to 59 months. The unit of randomization will be the outpatient therapeutic feeding center. The 10 health centers supported by UNICEF will be stratified by size ( $\pm 500$  admissions per site), and centers within a stratum will be randomized in a 1:1 ratio to one of two schedules of treatment: (1) standard weekly visits or (2) monthly visits with support for home-based surveillance.

Distribution of the therapeutic feeding rations, as well as medical and anthropometric surveillance, will take place on a weekly or monthly basis until discharge according to the random assignment of the site. Caregivers in the monthly visit group will receive additional instruction at admission regarding home-based MUAC measurement and clinical surveillance.

Regardless of intervention assignment, all children with uncomplicated SAM will receive standard medical care on admission as per national guidelines, and a home visit 3 months following discharge from the nutritional program. Additional data collection, including coverage assessment and economic costing analysis will be used to address the secondary objectives related to the evaluation of coverage and cost-effectiveness, respectively.

#### 3.2 Study setting

The study is proposed to take place in the Binji and Wamako local government areas (LGA) within Sokoto state of Northwestern Nigeria. This location represents a reasonable location for this study within an on-going nutritional program. As the study will be conducted over an extended period of time, the relative stability of this location is also expected to provide secure, uninterrupted access to the study population for monitoring and data collection. Finally, this setting includes a rural area largely representative of the Sahel region with endemic acute malnutrition and medium population density, where a reduced schedule of follow up would be justified and provide an operational advantage. It also represents settings of chronic food security crisis, where the rates of malnutrition are important. In 2015, the National Nutrition and Health Survey reported a prevalence of Global Acute Malnutrition (GAM) and SAM of 14.2% and 2.7%, respectively, when measured by MUAC among children < 5 years of age in Sokoto. Evidence drawn from this chronic crisis can therefore be expected to provide evidence relevant to other settings of the Sahel and beyond.

The study will benefit from partnerships with Epicentre and UNICEF Nigeria – both of whom have extensive an established presence and experience in the study region, and will advise the study on local culture and customs.

#### 3.3. Study sites

Study activities will take place in 10 outpatient therapeutic feeding centers supported by UNICEF. The 10 outpatient therapeutic feeding centers will be staffed by research nurses trained to seek written informed consent and support data collection during all enrollment and follow-up visits. Children transferred for inpatient care will be followed by a research nurse until hospital discharge. Once medical complications are resolved, appetite has returned and/or edema is reduced, the child will resume treatment at the original outpatient therapeutic feeding center and study follow-up until program discharge.

### 3.4 Target population

The study subjects will be children newly admitted for the treatment of uncomplicated SAM at one of 10 outpatient therapeutic feeding centers.

The specific eligibility criteria for the treatment of uncomplicated SAM:

- age from 6 to 59 months
- MUAC < 115 mm and/or grade 1-2 edema
- Absence of current illness requiring inpatient care\*

\*As per current treatment protocols, children will be referred to inpatient care if presenting with lack of appetite, intractable/continuous vomiting, fever, hypothermia, lower respiratory tract infection, severe respiratory distress, any chest in-drawing, severe anemia (hemoglobin < 7 g/dl), skin infection or lesions requiring IM/IV treatment, altered consciousness, hypoglycaemia, convulsions, severe dehydration, presence of grade 3 edema.

The specific inclusion criteria for the study are:

- Eligible for new admission\*\* at one of the study outpatient therapeutic feeding centers
- Written informed consent of parent or legal guardian

\*\*New admissions include cases of relapse, where the child was previously successfully treated, discharged as cured and returns with a new episode of acute malnutrition within 2 months of discharge. New admission will include children transferred from inpatient care to outpatient care to continue treatment but does not include children transferred from another outpatient site. New admission does not include returned defaulters who were absent for 3 consecutive visits before recovery and return to continue treatment.

The specific exclusion criteria for the study are:

- History of allergy to peanuts
- Any other condition in which, in the judgment of the Field Investigator, would interfere with or serves as a contraindication to protocol adherence or the ability to give informed consent\*\*\*

\*\*\*While determining eligibility, study staff will be asked to use good clinical judgment in considering a participant's overall suitability for inclusion. Some participants may not be appropriate for the study even if they meet all inclusion criteria. For instance, medical,

occupational or other conditions of the participant or parent/guardian may make routine home visits and evaluation difficult or make the child a poor candidate for retention. Any such potential exclusion must be validated by the Field Investigator.

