### 3.6 Random allocation and concealment

The reduced schedule of follow-up will be tested using a stratified cluster randomized design, with the health center as the unit of randomization. All children admitted for outpatient therapeutic feeding at a participating health center will receive the same schedule of follow-up.

Health centers will be stratified by size according to the number of admissions per site in order to promote balance of the intervention among children. Centers within a stratum will be randomized in 1:1 ratio to standard weekly vs. monthly follow-up. Randomization assignment will be made by lottery, in which a local representative will select the name of one of the two interventions from an envelope or opaque jar.

The study will be open, as it will not be possible to blind participants or study staff to frequency of follow up received.

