### 4.3 Evaluation of eligibility

Evaluation of eligibility will occur at the time of first visit/admission to the study outpatient therapeutic feeding centers. Upon arrival, program staff will screen children for eligibility for outpatient treatment as per standard protocol (e.g. age 6 to 59 months; MUAC < 115 mm or grade 1-2 edema; and absence of illness requiring inpatient management). Anthropometry (weight to the nearest 100 g; length (children <24 months) or stature (children ≥ 24 months) to the nearest 0.1 cm; and MUAC to the nearest 0.1 cm using the UNICEF band) will be assessed by program staff using standard techniques described for the WHO Multicenter Growth Reference Study. All study and program staff will be trained and standardized prior to beginning data collection. Standardization sessions will be repeated every 3 months during data collection. Children ineligible for outpatient treatment will not be admitted for nutritional therapy and asked to return home, with explanation of the program admission criteria. These children may be referred to the primary pediatric care program or vaccination program, as needed.

If the child is eligible for outpatient treatment, a study nurse will evaluate the specific study inclusion and exclusion criterion (e.g. new admission, no peanut allergy). If a child presenting to a site assigned to weekly follow-up is eligible for SAM treatment but found ineligible for study inclusion, the child will receive all medical and nutritional treatment with standard weekly follow up at the same site without participating in study data collections. If a child presenting to a site assigned to monthly follow-up is eligible for SAM treatment but does not participate in the study (e.g. parent declines to provide consent or child does not meet inclusion criteria), the child will receive all medical and nutritional treatment with standard weekly follow up at the same site without participating in study data collections. Non-participating children seeking care at sites assigned to monthly follow-up will receive standard care, while all other eligible and participating children included at the monthly site will continue to receive the alternative monthly follow-up as per the random assignment of the site.

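### At centers whose arm is openly known, Section 3.4 allows eligible children to be excluded for expected poor retention, which permits selection on a predictor of recovery, of unknown direction and size

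*Protocol*

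**What the plan says.** Protocol 3.6 describes a "stratified cluster randomized design, with the health center as the unit of randomization" and states: "The study will be open, as it will not be possible to blind participants or study staff to frequency of follow up received". Section 4.3 fixes the timing of screening: "Evaluation of eligibility will occur at the time of first visit/admission to the study outpatient therapeutic feeding centers". That section speaks throughout of sites already assigned to weekly or monthly follow-up.

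The note to the exclusion criteria in 3.4 says: "Some participants may not be appropriate for the study even if they meet all inclusion criteria". The example grounds are medical, occupational or other conditions of the child or guardian that "may make routine home visits and evaluation difficult or make the child a poor candidate for retention". The control is: "Any such potential exclusion must be validated by the Field Investigator". No threshold is given, and nothing requires the ground to be applied alike in both arms.

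Section 2.0 lists defaulting as a secondary endpoint, and 4.9 names default as a type of discharge alongside recovered and non-recovered. Section 4.8 counts a default after one missed visit in the monthly group and after three consecutive missed visits in the weekly group.

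On children who do not take part, 3.6 says: "All children admitted for outpatient therapeutic feeding at a participating health center will receive the same schedule of follow-up". Section 4.3 says: "Non-participating children seeking care at sites assigned to monthly follow-up will receive standard care", which there means weekly visits and no study data collection. Section 5.3 repeats this for families who do not consent.

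**The concern.** When clusters are randomized first and individuals are recruited afterwards by people who know the allocation, individual allocation is not concealed. Fixed entry criteria that are neutral to the arm are then the main protection against recruitment bias. The note in 3.4 loosens that protection on a sensitive variable, namely how likely the family is to stay in follow-up. A child expected to default is also less likely to be discharged as recovered, so the ground for exclusion is a likely predictor of the primary outcome as well as of a secondary one.

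If the ground is used more in one arm than in the other, the enrolled groups differ before treatment starts. The intention-to-treat principle in 3.9 covers enrolled children only, and excluded children leave the study data. In a non-inferiority comparison with a 5-point margin, a shift of one or two points matters in either direction.

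A separate matter is whom the results describe. Section 1.1 motivates the schedule by places where getting to a facility is difficult, and 1.2 wants results that carry over to settings where the standard protocol is impractical. A clause that screens out families who are hard to visit or retain works against that aim even if both arms apply it equally.

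**Working it through.** **Inputs from the protocol (3.7):** weekly recovery 0.80, margin −0.05, intraclass correlation 0.002, one-sided 0.05 score test, 350 children per center, 20% loss to follow-up. Ten centers at 1:1 give 5 per arm.

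**Assumed inputs (not in the documents):** the net extra share x of otherwise eligible children excluded in one arm only, and their recovery r had they been enrolled.

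**1. The plan's own figure.** Effective size per arm is n = 5m / (1 + (m − 1) × ICC). With m = 350 and ICC 0.002, n = 1750 / 1.698 = 1031. The Farrington-Manning score test at equal recovery of 0.80 then gives power 0.883. For ICC 0.001 and 0.01 it gives 0.938 and 0.538. The plan states 0.88, 0.94 and 0.54, so its table reproduces with 350 children analysed per center. With 20% loss, m = 280, n = 1400 / 1.558 = 899 and power is 0.84. That smaller size is used below.

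**2. Shift in one arm's recovery.** Removing a share x with recovery r from a group recovering at 0.80 gives

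shift = (0.80 − x·r) / (1 − x) − 0.80 = x(0.80 − r) / (1 − x).

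For x = 0.05 and r = 0.50: 0.05 × 0.30 / 0.95 = 0.0158.

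| Net extra exclusion in one arm | r = 0.40 | r = 0.50 | r = 0.60 |
|---|---|---|---|
| 1% | 0.4 points | 0.3 points | 0.2 points |
| 5% | 2.1 points | 1.6 points | 1.1 points |
| 10% | 4.4 points | 3.3 points | 2.2 points |

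The shift favours whichever arm excludes more. With equal exclusion in both arms it is zero in this model.

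**3. Effect on the non-inferiority decision (n = 899 per arm).** The probability of declaring non-inferiority is Φ[(observed difference + 0.05 − 1.645·s0) / s1], where s0 is the score-test standard error under the null and s1 the standard error under the actual proportions.

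- *More exclusion at monthly sites, true difference −0.05.* A bias of 2 points gives (0.02 − 1.645 × 0.0194) / 0.0194 = −0.61, a probability of 0.27. Biases of 1 and 3 points give 0.13 and 0.47. The nominal value is 0.05.
- *More exclusion at weekly sites, true difference 0.* A shift of 1.6 points gives (0.0342 − 1.645 × 0.0186) / 0.0186 = 0.19, so power falls from 0.84 to about 0.58. Shifts of 0.3 and 3.3 points leave 0.80 and 0.23.

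**4. Which direction the text suggests.** Pointing to more exclusion at monthly sites: a single missed visit is a default there (4.8). Pointing to more exclusion at weekly sites: attendance is weekly for up to 12 weeks, against visits at weeks 4, 8, 10 and 12 in the monthly group (4.6), so an occupational barrier weighs more there. Neutral: both groups get the unannounced home visit within two weeks (4.7), the same tracing of missed visits (4.8) and the same post-discharge visit (4.9). The text does not settle the sign.

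**The case against.** A reader might infer that staff will exclude more children at monthly sites, because those children go unseen for four weeks, and that the bias therefore favours a false non-inferiority conclusion. The documents do not support this. Both groups receive an unannounced home check of MUAC, edema and clinical condition within two weeks, missed visits are traced alike, and the heavier attendance in the weekly arm could push exclusion the other way. The consent rule does not settle it either. Declining changes the schedule only at monthly sites, but nothing says whether the children of those who decline have a better or worse prognosis.

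It can also be said that staff do not decide alone. One Field Investigator, who supervises all sites (6.0), validates each such exclusion, and this should limit divergence between centers. That stands as a partial safeguard. It is not a full one, because that role also knows each center's arm and has no arm-neutral rule to apply.

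The exclusion shares and the recovery of excluded children are assumptions. At 1% the shift is only about 0.3 points. The size also depends on defaulters counting as not recovered, which 4.9 suggests but the protocol does not spell out for the primary analysis.

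A further stronger reading is that the clause removes hard-to-reach families as a group. It does not say so. It names medical, occupational or other conditions, case by case, and does not mention distance, insecurity or nomadic life. What stands is that families who are hard to visit or retain fit its wording.

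**Conclusion.** The point holds as a design weakness. The protocol permits selection, after the arm is known, on a likely predictor of recovery, with validation by an unblinded role as the only control. It does not show that such selection will differ by arm, so neither a direction nor a size can be claimed.

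If one arm excludes a net extra 1% to 10% of children and half of them would have recovered, that arm's recovery moves by 0.3 to 3.3 points against the 5-point margin. Depending on which arm it is, this either raises the false non-inferiority rate or costs power. These figures rest on the assumed shares and recovery and on default counting against recovery. The loss of generalizability does not require any difference between arms.

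The conflict between 3.6 and Sections 4.3 and 5.3 on the schedule of non-participants is a separate matter of wording, and it stands whatever is thought of the bias.

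**What to change.** 1. In the exclusion note of 3.4, delete difficulty of home visits and poor prospects of retention as grounds for exclusion. Keep only objective, arm-neutral exclusions, such as the listed peanut allergy and a documented contraindication.
2. Keep a screening log, and report the numbers screened and excluded, with reasons, by site and by arm, so that any difference in selection can be seen.
3. Reconcile the statement in 3.6 that all admitted children at a center share one schedule with 4.3 and 5.3, under which non-participants at monthly sites are followed weekly.

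Adjusting the primary model for admission MUAC, edema, age and sex may help precision and baseline imbalance. It does not repair this selection, because none of these variables measures the propensity to stay in follow-up.

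The cost is an amendment of wording and a simple log. The downside is somewhat more default and missing follow-up among children who would otherwise have been left out. The stated power calculation does not change unless the allowance for loss is revised.
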